# Integrating Behavioral Health and Primary Care (IBH-PC) to improve patient-centered outcomes in adults with multiple chronic medical and behavioral health conditions: study protocol for a pragmatic cluster-randomized control trial

**DOI:** 10.1186/s13063-021-05133-8

**Published:** 2021-03-10

**Keywords:** Behavioral health, Primary care, Multiple chronic conditions, Pragmatic trials, Randomized control trial

## Abstract

**Background:**

Chronic diseases that drive morbidity, mortality, and health care costs are largely influenced by human behavior. Behavioral health conditions such as anxiety, depression, and substance use disorders can often be effectively managed. The majority of patients in need of behavioral health care are seen in primary care, which often has difficulty responding. Some primary care practices are providing integrated behavioral health care (IBH), where primary care and behavioral health providers work together, in one location, using a team-based approach. Research suggests there may be an association between IBH and improved patient outcomes. However, it is often difficult for practices to achieve high levels of integration. The Integrating Behavioral Health and Primary Care study responds to this need by testing the effectiveness of a comprehensive practice-level intervention designed to improve outcomes in patients with multiple chronic medical and behavioral health conditions by increasing the practice’s degree of behavioral health integration.

**Methods:**

Forty-five primary care practices, with existing onsite behavioral health care, will be recruited for this study. Forty-three practices will be randomized to the intervention or usual care arm, while 2 practices will be considered “Vanguard” (pilot) practices for developing the intervention. The intervention is a 24-month supported practice change process including an online curriculum, a practice redesign and implementation workbook, remote quality improvement coaching services, and an online learning community. Each practice’s degree of behavioral health integration will be measured using the Practice Integration Profile. Approximately 75 patients with both chronic medical and behavioral health conditions from each practice will be asked to complete a series of surveys to measure patient-centered outcomes. Change in practice degree of behavioral health integration and patient-centered outcomes will be compared between the two groups. Practice-level case studies will be conducted to better understand the contextual factors influencing integration.

**Discussion:**

As primary care practices are encouraged to provide IBH services, evidence-based interventions to increase practice integration will be needed. This study will demonstrate the effectiveness of one such intervention in a pragmatic, real-world setting.

**Trial registration:**

ClinicalTrials.gov NCT02868983. Registered on August 16, 2016.

## Introduction

### Background and rationale {6a}

The chronic diseases that drive the majority of morbidity, mortality, and health care costs in America and around the globe are largely influenced by human behavior. Tobacco use, poor diet, alcohol and substance use disorders, and physical inactivity together account for 38% of all deaths in the USA [1]. Insomnia, anxiety, depression, stress, and non-adherence to recommended treatment contribute additional morbidity and mortality. The presence of both chronic medical and behavioral health conditions drive poorer outcomes and higher costs than either alone [2, 3].

Behavioral Health Care (BH) is a short-hand term representing a wide variety of services that have often been physically, operationally, and even ideologically isolated from one another. The working definition of BH for this study (modified from Baird, 2014 [4]) is mental health care, substance use disorder care, health behavior change, and attention to family and other psychosocial factors that affect a person or a family unit. Conditions addressed as part of BH include depression, anxiety, stress, insomnia, overeating, inactivity, smoking, medication non-adherence, chronic pain, problem drinking, substance use disorder, and family distress.

Behavioral health conditions can often be effectively managed, resulting in improved outcomes for patients, their families and the health care system. Several psychological and behavioral techniques, including Cognitive Behavioral Therapy [5–8] and the IMPACT collaborative care model [9], improve outcomes, best demonstrated for depression.

The majority of patients in need of BH are seen in primary care, but that setting has difficulty responding to the full set of needs. Forty percent of primary care patients have BH needs and the need is even higher among those with chronic medical conditions [10]. Although some primary care providers (PCPs) are skilled and effective at delivering BH [11], many do not have the training, time, or inclination [12]. High-quality BH is the single most difficult area of medical care for patients to access [13] and nearly 70% of the more serious behavioral health conditions in primary care are neither assessed nor treated [14].

The traditional approach to delivering BH in much of the world is for PCPs to refer patients to specialists (psychiatrists, psychologists, counselors, and therapists) outside the primary care setting. Unfortunately, high-quality services are often not available, the referral process is challenging, and treatment initiation rates are low, in part due to the perceived stigma of seeing a mental health specialist [15–17]. Communication between mental health specialists and PCPs is often hampered by confidentiality concerns, time constraints, legal restraints, transportation barriers, and traditional practice habits. Fifty percent to 90% of primary care referrals made to out-of-office mental health practitioners fail to result in an appointment [18]. Of those patients who do schedule an appointment, most never initiate care [19]. When care is initiated, most of that care is not evidence-supported [20].

In response to these barriers, many primary care practices have instituted co-located services in which a Behavioral Health Provider (BHP) such as a psychologist or counselor and PCP deliver care in the same location [21]. This model eliminates some of the barriers to access, but the BHP often operates independently from the PCPs with separate hours, space, appointment systems, and medical records. Often, there is little communication or shared records between the two disciplines. There is little evaluation of such interventions [22].

An alternative approach to delivering BH for primary care patients is Integrated Behavioral Health Care (IBH) in which the BHP is a full member of the practice who shares workspace, infrastructure, records and support systems, participates fully in the life of the practice, and collaborates closely with PCPs in patient assessment and management. Beyond co-location, IBH includes support for population management, protocol-driven evidence-supported care, guideline-based external referral, use of brief visits, systematic needs identification, and practice-wide approaches to patient engagement.

The working definition of IBH (adapted from Korsen, 2013 [23]) for this study is the care a patient receives when PCPs and BHPs use a collaborative system of care, rather than focusing on separate approaches. Its goals are better and more efficient care of mental health conditions, substance use disorders, and chronic medical illnesses; better recognition and management of life stressors, crises, and stress-related physical symptoms; improved health behaviors; and more thoughtful and efficient health care utilization. Research suggests there may be an association between IBH and patient outcomes [24].

For primary care practices to effectively shift from co-located services to IBH, a supported practice change process is required [4]. While IBH checklists identifying integration elements exist [23, 25], a comprehensive intervention that systematically combines practice redesign with quality improvement (QI) coaching, provider and staff education, and collaborative learning does not. The Integrating Behavioral Health and Primary Care study (IBH-PC) responds to this need by testing the effectiveness of a comprehensive practice-level intervention (the IBH-PC toolkit) designed to improve outcomes in patients with multiple chronic medical and behavioral health conditions by increasing a practice’s degree of behavioral health integration. We sought to deploy the toolkit in a broad array of primary care practices and test its impact on patient functional status as well as the practices’ level of integration. We chose a pragmatic randomized trial design to allow our analysis and conclusions to be both rigorous and applicable to a broad range of practices.

### Objectives {7}

#### Hypothesis

Increased integration of evidence-supported behavioral health and primary care, compared to simple co-location of providers, will improve patient-centered outcomes in patients with multiple chronic medical and behavioral health conditions.

#### Research questions

Does using the IBH-PC toolkit, a practice-level intervention, affect patient-centered outcomes in adults with multiple chronic medical and behavioral health conditions?Does using the IBH-PC toolkit affect the degree of practice-level behavioral health care integration in primary care practices?What factors support or impede successful integration of behavioral health care into primary care practices?What are the costs of implementing the IBH-PC toolkit?

### Trial design {8}

The IBH-PC study is a two-arm, parallel, superiority, pragmatic, cluster-randomized trial that treats patients as the units of analysis clustered within practices that are the units of intervention. Practices are assigned in a 1:1 allocation ratio.

## Methods: Participants, interventions, and outcomes

### Study setting {9}

The IBH-PC study takes place in 45 primary care practices across the United States (Fig. 1). Practices represent a diverse distribution of geographic regions, population densities (urban vs. rural), patient population size, specialty (family vs. internal medicine), community health centers, federally qualified health centers, nonprofit and for-profit organizations, resident training sites, and ownership (hospital or health system, academic, private).

**Fig. 1 Fig1:**
[figure not shown]
Integrating Behavioral Health and Primary Care (IBH-PC) clinical sites

### Eligibility criteria {10}

#### Study practices

Primary care practices are eligible to participate if they:
Have at least one PCP and at least one BHP onsite (co-located),Have at least 0.5 full-time equivalent BHPs licensed to practice independently,Commit to maintaining onsite BHP for the duration of the study,Provide the research team with access to electronic medical records (EMRs) to identify patients with specific medical and behavioral health conditions for recruitment,Are willing to complete survey instruments periodically throughout the study, andAre willing to be randomized to either the active or control arm.

For practices with more than 10% of their revenue generated by Medicare, at least one BHP per practice must be eligible to bill Medicare. Practices are ineligible if they are already undergoing, or plan to undergo, another QI initiative similar to the IBH-PC intervention or if they already have an advanced level of BH integration as evidenced by a total Practice Integration Profile score (PIP) above 75. The PIP is a survey of 30 items completed by primary care providers and staff about their own practice used to measure practice level integration [26, 27].

### Study patient participants

Patients are eligible to participate if they:
Are at least 18 years old,Are an active patient of a participating study practice as evidenced by at least two visits in a period of 24 months for any purpose, including at least one in the most recent 6 months,Are willing to complete three surveys over 2 years, andHave both an eligible chronic medical condition and an eligible chronic behavioral health condition, or at least three eligible chronic medical conditions. Eligible chronic medical conditions include arthritis; obstructive lung disease including emphysema, chronic bronchitis, or asthma; non-gestational diabetes; and heart disease manifested as heart failure or hypertension. Eligible behavioral health conditions include mood disorder (anxiety or depression), chronic pain (including headache, migraine, neuralgia, fibromyalgia, or chronic musculoskeletal pain), insomnia, irritable bowel syndrome, and substance misuse (substance use disorder, tobacco use, or problem drinking).

To determine patient eligibility, medical records are reviewed for a period of 24 months with the most recent date being within 12 months of the study start at each practice. Within this period, evidence of age, minimum number of visits, and medical and behavioral health conditions will be determined.

Evidence of medical conditions may take the form of a specific diagnosis on a problem list. Evidence of diabetes may also be indicated by 3 months of insulin or other diabetes medications (excepting metformin which is not specific to diabetes) or any hemoglobin A1C value greater than 6.4%. Evidence of heart disease may also be indicated by 3 months of cardiac medications specific to hypertension or heart failure (excepting beta-blockers and other medications with broader indications), or 3 sequential blood pressure measurements with mean systolic pressure > 140 mmHg or mean diastolic pressure > 95 mmHg.

Evidence of a behavioral health condition may take the form of a specific diagnosis on a patient’s problem list, 3 months of certain medications used for behavioral conditions (antidepressants, anxiolytics, opioids, antineuropathic agents, agents for alcohol use disorder or smoking cessation, etc.), or persistent failure to attain physiologic control of a medical problem evidenced as systolic blood pressure > 165 mmHg for 3 months or more or A1C > 9% for 6 months or more.

#### Who will take informed consent? {26a}

Eligible patient participants are identified by review of EMRs in each participating primary care practice [28]. Acting as trusted third party, the DARTNet Institute [29] reviews the EMR data, identifies potential patient participants, and offers participation.

Eligible patients are mailed a letter describing the purpose of the study and that, if they choose to participate, they are requested to complete a brief set of surveys at three timepoints via web, paper, or phone. The letter also describes the process to opt-out as well as provides a phone number to call for more information on the study. The DARTNet Institute follows-up the letters with phone calls to eligible patients. Consent is administered and documented by phone, paper, or via web at the completion of the baseline set of surveys. Participating patients provide consent to link their EMRs to survey data and may discontinue participation at any time. All study materials are available in both Spanish and English.

#### Additional consent provisions for collection and use of participant data and biological specimens {26b}

The study consent process includes permission for additional analyses of collected data. No biological specimens are collected.

### Interventions

#### Explanation of the choice of comparators {6b}

The active comparator (the intervention) is the use of the IBH-PC toolkit to support a practice-level change process. Use of the IBH-PC toolkit is intended to increase the delivery of highly integrated behavioral health and primary care, which is hypothesized to result in improved patient outcomes. The control comparator is co-location of a behavioral health provider within or adjacent to the primary care practice (at the same street address), without additional integration [12]. Co-location was chosen as the control comparator as it is highly prevalent in the field and has emerged as a standard of care in this domain [10].

#### Intervention description {11a}

The intervention, the IBH-PC toolkit, is a set of implementation strategies consisting of four components:
An online educational curriculum,A structured, team-based, practice redesign and implementation workbook,Remote QI coaching services for internal QI facilitators, andAn online learning community.

The purpose of the IBH-PC toolkit is to guide and support primary care practices through a practice change process as they work to increase their degree of behavioral health integration through, for example, improvement of screening, case identification, management, or follow-up. Progress through the toolkit and use of its components are expected to be variable among participating practices, taking from 9 to 24 months.

##### Online education curriculum

The IBH-PC toolkit includes an asynchronous online curriculum on evidence-based concepts of IBH and methods of applying them. The curriculum includes one interprofessional course for all practice member roles and seven individual courses, targeting different practice member roles (practice manager, BHP, PCP, nurse, staff, IBH-PC facilitator) Courses take approximately 4–14 h to complete, depending on the practice member role. The online curriculum is housed at the Arizona State University and is made available through an online learning management platform [30]. It is intended, but not required, that all practice members complete the courses appropriate for their roles.

##### Practice redesign and implementation workbook

The redesign and implementation process is available as a workbook format (.pdf format) that is posted in an online, shared workspace. Practices are encouraged to establish interdisciplinary project teams, with a practice member serving as project leader and an on-site, internal facilitator. The workbook directs the project team through four stages: study start up and leadership engagement, planning the scope and boundaries of workflow redesign using a Lean Management approach [31–33], redesigning workflow with recommended tactics, and implementing those changes in the practice. It is intended, but not required, that the project teams complete all stages sequentially.

##### Remote quality improvement coaching

To support the project teams through the redesign process, external QI coaches work with individual practices. Each study practice is assigned a team of two coaches who meet with them via phone or web-meeting throughout the practice redesign process (up to 24 months). The remote QI coaches are part of the research team based at the University of Vermont (UVM). It is intended, but not required, that all project teams meet with their coaches on a regular basis.

##### Online learning community

The IBH-PC toolkit includes an online forum and learning community created using an open source bulletin board system [34]. It provides a platform for practice members and other IBH-PC stakeholders to communicate with one another. Discussion topics vary and are primarily focused on practice member needs and interests. It is intended, but not required, that all project teams engage in the online learning community through regular participation by at least one team member.

#### Criteria for discontinuing or modifying allocated interventions {11b}

Study practices randomly assigned to the intervention are encouraged to use the IBH-PC toolkit completely and sequentially, as prescribed. However, practices may use the toolkit out of sequence, modify sections, or skip them completely. Given the low risk of this practice-level intervention, there are no early stopping rules.

#### Strategies to improve adherence to interventions {11c}

The IBH-PC toolkit is designed to encourage practice adherence to the intervention through engagement with a remote QI coaching team, access to continuing education credits as part of the online education curriculum, and creating a sense of community with standards of normal behavior through the online learning community.

#### Relevant concomitant care permitted or prohibited during the trial {11d}

Participating practices may not participate in other practice change projects similar to the IBH-PC toolkit during the trial. However, they may use QI and other strategies to improve any aspect of their practice they see fit, including improving BH services.

### Provisions for post-trial care {30}

Not applicable. The study represents a 24-month practice level-intervention, there is no need for post-trial care.

### Outcomes {12}

#### Research question 1: does using the IBH-PC toolkit, a practice-level intervention, affect patient-centered outcomes in adult patients with multiple chronic medical and behavioral health conditions?

##### Primary outcomes

Change in mean patient Patient-Reported Outcomes Measurement Information System [35] (PROMIS-29) scores from baseline to follow-up for eight domains:
Physical functionAnxietyDepressionFatigueSleep disturbanceSocial functioningPain intensityPain interference

##### Secondary outcomes

Change in other mean patient-reported measures of health and quality of care from baseline to follow-up.
Empathy [36]Medication adherence [37]Healthcare utilization [38]Time lost due to disability [39]Physical function [40]Patient centerednessChange in mean measures of patient disease control from baseline to follow-up for specific subgroups identified from EMRs.
Depression [41]Anxiety [42]Asthma symptoms [43, 44]Substance use disorder [45]Problem drinking [46]

#### Research question 2: does using the IBH-PC toolkit affect the degree of practice-level behavioral health care integration in primary care practices?

##### Secondary outcomes

Change in median PIP total score from baseline to follow-upChange in median PIP domain scores from baseline to follow-up
Practice WorkflowClinical ServicesIntegration MethodsCase IdentificationPatient EngagementWorkspace Arrangement and Infrastructure

#### Research question 3: what factors support or impede successful integration of behavioral health care into primary care practices?

##### Secondary outcomes

Identification of practice characteristics and external factors supporting or impeding integration as measured by changes in PIP scores.

#### Research question 4: what are the costs of implementing the IBH-PC toolkit?

##### Secondary outcomes

Total estimated costs of using the IBH-PC toolkit over a period of 24 months, excluding the costs and revenues associated with ongoing clinical operations.

##### Participant timeline {13}

Practices are screened on a rolling basis for study eligibility and will therefore have varying randomization and study start dates. Moreover, it is anticipated that practices will move through the IBH-PC toolkit at different rates. Therefore, the timeframes represented in Fig. 2 are anticipated averages across all study practices.

**Fig. 2 Fig2:**
[figure not shown]
Study timeline

### Sample size {14}

Sample size calculations were adjusted for the cluster randomized design [47]. To achieve a nominal significance level of 0.05 for the main hypothesis that any one or more of the eight PROMIS primary outcomes achieves significance, we will apply the Bonferroni correction [48] requiring *P* < 0.05/8 = 0.00625. All PROMIS domain scales are normalized to a standard deviation of 10 points [35]. We assume that the within-practice correlations of the PROMIS scales are 0.03 (similar to the SF-12 [49]). Although minimally important differences [50] are not fully specified, they range from 2 to 8 points for other instruments in the PROMIS series [51, 52].

Power calculations were conducted prior to study recruitment assuming 75 subjects from 40 practices, giving the study 3000 subjects and 90% power to detect a difference in any of the 8 PROMIS scales of 2.5 points or more. With 45 practices recruited, 43 practices randomized to intervention or control, and 2 practices considered as “Vanguard” the study recruitment meets these power and sample size expectations.

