### Statistical methods

#### Statistical methods for primary and secondary outcomes {20a}

Research question 1: does using the IBH-PC toolkit, a practice-level intervention, affect patient-centered outcomes in adults with multiple chronic medical and behavioral health conditions?

For the primary outcomes, we will use generalized linear mixed (GLM) models [64] of patient health status (PROMIS-29 scales) to perform intention-to-treat analyses [65] as a function of experimental condition (active vs. control) and patient characteristics, with patients clustered within practices. The parameters of interest are the central tendency (mean), statistical significance (*P* values), and 95% confidence intervals (CI) of the adjusted change in PROMIS-29 domain from baseline to follow-up. Each of the 8 outcome domains in the PROMIS-29 will be modeled individually as 8 separate hypotheses with adjustment for multiple comparisons and for clustering within practices.

Patient characteristics will be measured at baseline and will include age, gender, race, ethnicity, marital status, employment, education, and income.

For secondary patient outcomes, including change in other patient-reported measures of health and quality of care, and measures of patient disease control from baseline to follow-up, we will use similar GLM models as above but will not adjust for multiple comparisons.

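### Single-step Bonferroni across the eight PROMIS-29 domains is valid but gives up domain-level power that Holm would keep at the same familywise error; the 95% intervals need a label

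*Protocol article*

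**What the plan says.** Under Sample size {14}, the protocol article gives the aim of the correction: "To achieve a nominal significance level of 0.05 for the main hypothesis that any one or more of the eight PROMIS primary outcomes achieves significance". To meet it, "we will apply the Bonferroni correction", with the threshold worked out as 0.05/8 = 0.00625. No step-down or other sequential rule is mentioned.

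Under Statistical methods for primary and secondary outcomes {20a}, each domain "will be modeled individually as 8 separate hypotheses with adjustment for multiple comparisons and for clustering within practices". The method of adjustment is not named again there, so the only one on record is the Bonferroni rule from {14}. The same paragraph lists among the quantities to be reported "statistical significance (*P* values), and 95% confidence intervals (CI) of the adjusted change in PROMIS-29 domain from baseline to follow-up". It does not say whether the 95% level applies to each domain separately or to the eight jointly, nor that a verdict is read from an interval.

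**The concern.** The two sections serve different questions. Section {14} protects one global claim, that the toolkit affects at least one domain. Section {20a} sets up eight domain-level claims, and the Discussion counts learning about effects on several domains of health among the design's strengths. For the global claim, single-step Bonferroni does the job. For the domain-level claims, it holds every domain to 0.00625 even after other domains have been rejected, although error control does not require this. Holm relaxes the threshold after each rejection and keeps the same familywise guarantee whatever the dependence between domains. At stake are second and later domains that truly improve but are reported as not significant.

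A smaller reporting matter goes with it. If the 95% intervals are ordinary per-domain intervals, a domain can have an interval that excludes zero while its P value misses 0.00625. Without a label, a reader may take such an interval as a positive result.

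**Working it through.** **Inputs.** From {14}: SD 10 ("All PROMIS domain scales are normalized to a standard deviation of 10 points"), within-practice correlation 0.03, 40 practices of 75 patients, eight domains, familywise level 0.05. From Trial design {8}: 1:1 allocation, hence 1500 patients per arm. Assumed, because the article does not give them: two-sided tests, equal correlation of 0.3 to 0.6 between domain test statistics, and no variance reduction from baseline adjustment.

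**The plan's threshold.** 0.05/8 = 0.00625 is exact. For eight independent tests the familywise error is 1 − (1 − 0.00625)^8 = 0.0489, so the rule is valid.

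**Standard error.** Design effect = 1 + (75 − 1) × 0.03 = 3.22. Effective n per arm = 1500/3.22 = 465.8. SE = 10 × √(2/465.8) = 0.655 points.

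**Stated power.** The article gives 90% at 2.5 points. With this SE, 2.5/0.655 = 3.815, and two-sided at 0.00625 the critical value is 2.734, so power = Φ(3.815 − 2.734) = 86.0%. A one-sided 0.00625 test gives 90.6%, and a two-sided test with an assumed baseline correlation of 0.3 gives 89.7%. Sidedness is not stated, so the 90% is reachable and is not challenged here. It does mean that 0.655 is a derived figure; a two-sided 90% would imply an SE of 2.5/(2.734 + 1.282) = 0.62.

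**Holm thresholds, smallest P first.** 0.00625, 0.00714, 0.00833, 0.01, 0.0125, 0.01667, 0.025, 0.05. The first equals the Bonferroni threshold, so the two methods must agree on whether any domain is significant.

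**Per-domain power.** Simulation of eight equicorrelated normal statistics with mean d/0.655 in the improving domains, 400,000 trials per setting, correlations 0.3 and 0.6:

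| Domains improving | Effect (points) | Bonferroni | Holm |
|---|---|---|---|
| 8 | 2.0 | 62% | 73–75% |
| 4 | 2.0 | 62% | 66% |
| 8 | 2.5 | 86% | 93–94% |
| 4 | 2.5 | 86% | 88–89% |
| 1 | 2.0 or 2.5 | 62–63% or 86% | the same to within 0.1 point |

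The probability of at least one rejection was identical under both methods in every setting. Familywise error under the global null was also identical (3.6–4.6%). With four domains improving by 2.0 points, Holm uses more of the allowance, 3.1–3.7% against 2.1–2.4%, and stays below 5%.

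**Intervals.** A per-domain 95% interval excludes zero once the estimate exceeds 1.960 × 0.655 = 1.28 points in absolute value. P < 0.00625 needs 2.734 × 0.655 = 1.79 points. Between these the interval excludes zero and the Bonferroni threshold is missed. With no true effect anywhere and independent domains, at least one of eight lands in that zone with probability 1 − (1 − 0.04375)^8 = 30%; at correlation 0.5 it is 24%. For one domain with a true effect of 2.5 points the probability is 96.8% − 86.0% = 10.8%.

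**The case against.** The strongest reply is that nothing is misstated. The correction is tied to the global hypothesis, where Holm and Bonferroni always agree. A valid, prespecified and correctly computed rule is not wrong because a stepwise variant exists. This stands: Bonferroni here is inefficient, not erroneous, and a reader should not infer that error control fails or that the main hypothesis loses power. It does not dispose of the point, because {20a} makes each domain a hypothesis in its own right.

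The second reply is that the largest gains need all eight domains to improve equally. This also stands. The gain falls to 2–4 points with four improving domains and to nothing with one, and the correlations are assumed. An effect across many domains is plausible for a practice-wide intervention, but the article does not establish it.

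Third, a reader might infer that the 95% intervals contradict the 0.00625 rule. The article does not support that. The P value is the stated decision rule, {20a} promises multiplicity adjustment in the same paragraph, and intervals used for estimation commonly sit beside an adjusted P threshold. What remains is an unlabelled interval level, which an analysis plan not shown may already settle.

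Fourth, Bonferroni buys something. It has simple matching simultaneous intervals, at 99.375% (2.734/1.960 = 1.395 times as wide as 95%). Holm has no such simple match: every extra domain that it rejects has P of at least 0.00625, so its 99.375% interval would include zero. This stands and shapes the fix.

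Last, follow-up was complete when the article was published and the arms are not blinded, so moving to a more permissive rule needs care over timing.

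**Conclusion.** The point holds as an avoidable loss of efficiency for second and later domains. Holm never loses a domain that Bonferroni claims and keeps familywise error at or below 0.05. It adds about 11–13 percentage points of per-domain power if all eight domains improve by 2.0 points, 7–8 at 2.5 points, 2–4 if four improve, and none if only one does. These figures rest on the derived SE of 0.655, two-sided tests and the assumed correlations. That Holm rejects at least as many domains rests on none of them. The interval issue is a matter of labelling. The change is worth making, but the primary analysis is sound without it.

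**What to change.** In {14} and {20a}, replace Bonferroni with Holm: smallest P value against 0.05/8, next against 0.05/7, and so on, stopping at the first failure. State that domain verdicts come from Holm-adjusted P values. Keep 0.00625 as the first step, so that the sample-size basis and the global verdict are unchanged. Keep the 95% intervals, label them as per-domain and not adjusted for multiplicity, and say that verdicts are not read from them. Do not present 99.375% intervals as matching Holm verdicts.

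The cost is a sentence or two in each section, plus a dated, justified amendment. Under Trial status, data processing was under way and no results were reported, so the amendment must be on record before outcomes are examined by arm. If that point has passed, keep Bonferroni as the prespecified rule and add only the interval label. The lasting downside is that Holm offers no simple simultaneous intervals to set beside its verdicts.
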